
##### Predictors/moderators of treatment outcome regarding ODD/CD symptoms and impairment

As moderators or predictors of treatment outcome at T4 regarding ODD/CD symptoms and impairment, the following variables will be analyzed: (1) sociodemographic variables (e.g. place of residence, socioeconomic status; education, income, occupation and age of parents/caregivers; number of children in the family), which will be assessed through parent/caregiver interview at T1, (2) severity of comorbid disorders at T1-T3 using the patient- and parent-rated SCL-ADHD, the parent-rated CBCL/6-18R, and the teacher-rated TRF/6-18R (see above), (3) specific psychological traits of the parents/caregivers (parental aggression, depression and stress) at T1 and T3 using the FB-Ä and DASS (see above), (4) specific psychological traits of the patient (intelligence), assessed at T1 using the German version of the Culture Fair Intelligence Test, Primary Intelligence Scale 1 (CFT 1-R) [54] and Scale 2 (CFT 20-R) [55].

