In detail, this study will examine the following hypotheses:1) The experimental group (THAV/ScouT + AUTHARK) will show stronger adherence (implementation of therapy homework assignments (THA)) than the control group (THAV/ScouT), as assessed after each therapy session using the Questionnaire for Therapy Adherence [42] (primary outcome).2) The experimental group (THAV/ScouT + AUTHARK) will show a stronger reduction in aggressive symptoms than the control group (THAV/ScouT) (assessed using the parent-, teacher-, and patient-rated DISYPS-III Symptom Checklist for Disruptive Behavior Disorder (SCL-DBD parent, SCL-DBD teacher, SCL-DBD patient (ages 11–18) [43] and using the individual problem list from the THAV program [4]).3) The experimental group (THAV/ScouT + AUTHARK) will show a stronger reduction in comorbid symptoms than the control group (THAV/ScouT) (assessed using the total score of the German version of the Child Behavior Checklist for ages 6–18 (CBCL/6-18R-total) [44], the total score of the German version of the Teacher’s Report Form for Ages 6–18 (TRF/6-18R-total) [45], the total score of the German version of the Youth Self Report for ages 11–18 (YSR/11-18R-total) [46], and the parent-, teacher-, and patient-rated DISYPS-III Symptom Checklist for Attention-Deficit/Hyperactivity Disorder (SCL-ADHD parent, SCL-ADHD teacher, SCL-ADHD patient (ages 11–18) [43]).4) Patients in the experimental group (THAV/ScouT + AUTHARK) will show a stronger improvement in psychological functions that help to reduce aggressive symptoms (social-cognitive information processing, impulse control, social skills, empathy) than patients in the control group (THAV/ScouT) (assessed using the parent- and patient-rated Questionnaire on Aggressive Behavior in Children (FAVK parent, FAVK patient (ages 9–12) [47], the parent- and patient-rated Inventory of Callous-Unemotional Traits (ICU parent, ICU patient (ages 8–12) [48] [49], and a Social Problem-Solving Test for children ages 6–12 (SPST) [7].5) Patients in the experimental group (THAV/ScouT + AUTHARK) will show a stronger improvement regarding psychosocial functioning and quality of life than patients in the control group (ScouT/THAV) (assessed using the parent-rated modified German version of the Weiss Functional Impairment Rating Scale Parent Report (WFIRS-P-M) [6], the revised parent- and patient-rated Questionnaire for Measuring Health-Related Quality of Life in Children and Adolescents KINDL-R parent, KINDL-R patient (ages 7–13) [50], and the parent- and patient-rated Questionnaire for the Assessment of Adaptive and Maladaptive Emotion Regulation Strategies (FRUST parent, FRUST patient (ages 8–12)) [51].6) Patients and parents/caregivers in the experimental group (ScouT/THAV + AUTHARK) will show higher treatment satisfaction than those in the control group (ScouT/THAV) (assessed using the modified German version of the Client Satisfaction Questionnaire (ZUF-8-M) for parents/caregivers and patients [52]).

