## Methods

### Trial design

The AUTHARK study is designed as an interventional randomized controlled study with two parallel treatment arms.

Figure 1 shows the overall design of the AUTHARK study. After the initial screening at T1, patients who meet the inclusion criteria will be randomly assigned to one of the treatment arms. Children in both the experimental group and the control group will receive social skills training (combination of THAV [4] and ScouT [7]). In addition to the treatment, the AUHARK smartphone app will be used in the experimental group. The treatment will be administered in three phases (1–3). Each phase includes eight weekly therapy sessions with the children and two to three sessions with the parents/caregivers. The first treatment phase (1) is followed by an intermediate assessment (T2) with a reduced set of assessment instruments. The second treatment phase (2) is followed by a major assessment (T3). Children who no longer show clinically significant symptoms of ODD/CD at T3 will not receive further therapy but will participate in a first follow-up assessment (T4) eight weeks after T3. Those patients with significant symptoms at T3 will undergo a third treatment phase with a further eight child sessions and two to three caregiver sessions, which will be followed by the T4 assessment. A follow-up evaluation (T5) for all patients will take place one year after T4.

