##### Secondary outcomes

As a secondary Outcome, we will analyze the quantity (relative ratio) and the overall quality rating separately. Additionally, the percentage of tokens received from the therapists for homework compliance will be considered as a secondary outcome measure.

Further secondary outcomes listed below will be assessed at T1 (baseline) and at T3 or T4:Parent-, teacher-, and patient-rated symptoms of ODD/CD, which will be assessed using the respective rating scales: the parent-, teacher-, and patient-rated DISYPS-III Symptom Checklist for Disruptive Behavior Disorder (SCL-DBD parent, SCL-DBD teacher, SCL-DBD patient (ages 11–18)) [43]. Reliability and validity as well as the sensitivity to change of these scales have already been proven in German samples [43].Clinician-rated symptoms of ODD/CD using the Structured Interview for Disruptive Behavior Disorder (ILF-EXTERNAL), which is part of the comprehensive Structured Interview for Children and Adolescents according to ICD-10 and DSM-5 from the DISYPS-Systems (DISYPS-ILF) [53].Overall behavioral and emotional problems assessed using the total score of the German version of the Child Behavior Checklist for ages 6–18 (CBCL/6-18R-total) [44], the total score of the German version of the Teacher’s Report Form for ages 6–18 (TRF/6-18R-total) [45], and the total score of the German version of the Youth Self Report for ages 11–18 (YSR/11-18R-total) [46]. Reliability and validity as well the sensitivity to change of the German versions of these scales have been demonstrated in several studies [44].Triggering and maintaining components of aggressive behavior (social-cognitive information processing, impulse control, social skills, and reactions to the social environment) assessed using the parent- and patient-rated Questionnaire on Aggressive Behavior in Children (FAVK parent, FAVK patient (ages 9–12) [47].Parent-rated satisfaction with the treatment, assessed using the modified German version of the Client Satisfaction Questionnaire (ZUF-8-M parent), and patient-rated satisfaction with the treatment, assessed using the modified German version of the Client Satisfaction Questionnaire (ZUF-8-M patient) [61], which has been shown to be reliable, valid, and sensitive to change [62].

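### Comorbidity and parental measures taken after randomization are listed as moderators or predictors of T4 outcome without separating the two roles; moderation should use T1 values only

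*Protocol article*

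**What the plan says.** The section Predictors/moderators of treatment outcome opens with one joint label: "As moderators or predictors of treatment outcome at T4 regarding ODD/CD symptoms and impairment, the following variables will be analyzed". Four groups of variables follow. Sociodemographic variables and intelligence are fixed at T1. The other two groups are not:

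- Comorbidity: "severity of comorbid disorders at T1-T3 using the patient- and parent-rated SCL-ADHD, the parent-rated CBCL/6-18R, and the teacher-rated TRF/6-18R".
- Parents: "specific psychological traits of the parents/caregivers (parental aggression, depression and stress) at T1 and T3".

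Trial design sets the order of events: "After the initial screening at T1, patients who meet the inclusion criteria will be randomly assigned to one of the treatment arms". T2 and T3 therefore fall after allocation and after treatment phases 1 and 2.

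Hypothesis 3 in the Background says that the app arm "will show a stronger reduction in comorbid symptoms than the control group", measured with the CBCL, TRF and SCL-ADHD. The CBCL and TRF totals are also secondary outcomes, under the rule "Further secondary outcomes listed below will be assessed at T1 (baseline) and at T3 or T4". SCL-ADHD, FB-Ä and DASS are supplementary outcomes measured before and after treatment.

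Mediators of change is a separate list (fidelity, therapeutic relationship, parent-rated emotion regulation, adherence). It contains none of these five scales. Analyses of secondary endpoints plans moderation by interaction and simple slopes.

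**The concern.** A moderator answers the question of which children gain more from the app. Randomization protects that comparison only within groups defined before allocation. A T3 comorbidity score is, by hypothesis 3, partly a result of the app. App and control children with the same T3 score are then not alike at baseline: if the app works, the app child will tend to have started worse or had a less favourable course. The app effect at a given T3 score mixes the effect sought with this selection, and it holds fixed part of what the app is meant to change.

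Moderators and predictors are a stated research question of the trial, and the pilot is meant to prepare a multicenter trial. An early response to treatment could be reported as a characteristic of children who respond.

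**Working it through.** **Side by side.** The later time points are written into the list, in contrast to the two groups fixed at T1, so this is more than a detail left to an analysis plan. Nothing in the moderator section restricts moderation to T1, and the mediator list does not take up the T2/T3 values. Following the text as it stands permits a group × T3-severity interaction with simple slopes. Two details narrow the point. Participant timeline limits T2 to parent and child questionnaires, so the teacher-rated TRF can have only T1 and T3 values. Parental traits are named at T1 and T3, not T2.

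**Size.** The plan gives no figure for these analyses, so there is none to reproduce. The sample-size figure (35 per arm; 30/0.90 = 33.3 and 30/0.85 = 35.3) has no bearing here.

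Inputs from the protocol article: an effect of 0.4 SD and about 30 children per arm (Sample size). The 0.4 is borrowed, since it is not stated for ODD/CD symptoms at T4. Everything else is assumed:

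- correlation of 0.5 between baseline severity and both T3 severity and T4 outcome, leaving residual variance 0.75;
- share c of that residual variance common to T3 and T4: 0, 0.3 or 0.6;
- app effect a on T3 severity: 0, 0.2 or 0.4 SD;
- SD t of a child-specific app effect, unrelated to baseline severity: 0, 0.5 or 0.8;
- app effect e on T4 outcome: a reduction of 0.4 or 0 SD.

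There is no true moderation by baseline severity.

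Formulas, regressing T4 outcome on group, T3 severity and their product:

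- slope in the control arm: b0 = 0.25 + 0.75c
- slope in the app arm: b1 = (b0 + t²)/(1 + t²)
- app effect at the overall mean of T3 severity: −e + a(b0 + b1)/2
- interaction: b1 − b0 = t²(1 − b0)/(1 + t²)

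| c | t | b0 | b1 | a=0.4, e=0.4 | a=0.2, e=0.4 | a=0.4, e=0 | interaction |
|---|---|---|---|---|---|---|---|
| 0 | 0 | 0.25 | 0.25 | −0.30 | −0.35 | +0.10 | 0 |
| 0 | 0.8 | 0.25 | 0.54 | −0.24 | −0.32 | +0.16 | 0.29 |
| 0.6 | 0 | 0.70 | 0.70 | −0.12 | −0.26 | +0.28 | 0 |
| 0.6 | 0.5 | 0.70 | 0.76 | −0.11 | −0.25 | +0.29 | 0.06 |
| 0.6 | 0.8 | 0.70 | 0.82 | −0.10 | −0.25 | +0.30 | 0.12 |

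A simulation of one million children per setting gave the same values within sampling error. The results are:

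- With a true effect of −0.40 and a = 0.4, between 0.10/0.40 = 25% and 0.303/0.40 = 76% of the effect is missing from the conditional estimate.
- If the app lowers T3 severity but leaves T4 outcome unchanged, a false effect of 0.10 to 0.30 SD against the app appears.
- If a = 0, the conditional group effect stays at −0.40.
- The interaction is zero when t = 0, whatever a is. With t above 0 it is 0.06 to 0.29. In 1,500 simulated trials of 60 children per setting it was then significant at 5% in 5–24% of trials.
- With T1 severity as moderator, the app effect is at its true value, the interaction is zero, and the false-positive rate is 4–6%.

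A simpler product calculation gives a similar order. An app effect of 0.2 to 0.4 SD on T3 severity times an assumed path of 0.4 to 0.6 to T4 outcome is 0.08 to 0.24 SD, or 20–60% of 0.4. This too is attenuation of the conditional group effect, not bias in the interaction.

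**The case against.** The heading of the list covers predictors as well as moderators, and using T2 or T3 severity to forecast T4 status is not biased as a forecast. T3 symptom status even decides who receives the third treatment phase, so T3 severity is a natural non-causal predictor. This stands: a reader might infer that every result from this list will be biased, and the text does not support that.

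The percentages can also be over-read. They might be taken as a loss in the moderation result or in the trial's efficacy estimates. They are neither. A constant app effect leaves the interaction at zero. The app effect on ODD/CD symptoms comes from the mixed models or estimating equations planned for secondary endpoints, and nothing says that it will be read from a moderator model.

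A reader might also infer that the hypotheses predict an app effect on parental aggression, depression or stress. None of the six does, and being listed as a supplementary outcome is not a prediction. The parent sessions of THAV do address parents' thinking about their own aggression, but in both arms. T3 parental values are therefore measured during treatment, but an expected app effect is not established.

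Finally, nothing says that moderator results will select children for the multicenter trial. Sample size gives the pilot's purpose as estimating variance for a later power calculation.

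What remains is that the two roles are not separated, and the causal one is not confined to baseline values.

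**Conclusion.** The concern holds in conditional form. Used as moderators, T2/T3 comorbidity scores bias the conditional app effect and simple slopes whenever hypothesis 3 is true and those scores are related to T4 outcome. The interaction itself is distorted only if, in addition to that relation, the app effect varies between children, and this can occur even when mean T3 severity is unchanged. For FB-Ä and DASS at T3, only the general objection to post-randomization moderators applies.

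The ranges of 25–76% and 20–60% illustrate attenuation of a conditional group effect. They rest on assumed correlations, an assumed app effect on T3 severity, and a borrowed 0.4 SD; they do not measure what will happen in this trial. The analyses are exploratory, and the primary comparison of therapy homework adherence is untouched. The point is worth correcting because the ambiguity is in the text and baseline values avoid it.

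**What to change.** State in the moderator section, and carry into the analysis plan, that moderation analyses and baseline predictors use T1 values only: SCL-ADHD, CBCL, TRF, FB-Ä, DASS, intelligence and sociodemographic variables. Add that any use of T2 or T3 values is reported as non-causal prediction or, if wanted, as exploratory mediation, and is not interpreted as showing for whom the app works.

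There is no need to move all T2/T3 values to the mediator list. That would add mediation analyses to a 70-child pilot, and T3-to-T4 mediation would be entangled with the third treatment phase, which depends on T3 status.

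The cost is one or two sentences. The T1 values are already planned, and no visit, instrument or sample-size change is needed.

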##### Mediators of change

As one potential mediator, (1) treatment fidelity will be assessed using an adapted version of the THAV Integrity Questionnaire [71] and the ScouT Treatment Integrity Questionnaire [72], which measure treatment integrity throughout the whole treatment process. After each unit of THAV/ ScouT therapy, the therapist will record the percentage of time he/she spent implementing the specific therapy elements from the THAV or ScouT program. In addition, the therapist will document which materials (e.g., worksheets, therapeutic stories, etc.) were used during the treatment sessions. The THAV Integrity Questionnaire has shown satisfactory reliability scores [13] and the ScouT Treatment Integrity Questionnaire has shown excellent internal consistencies [14]. Moreover, as a possible mediator, we will measure the (2) therapist-patient relationship and therapist-caregiver relationship using the German Relationship Questionnaire for Child and Adolescent Psychotherapy (BeKi) [73]. In order to assess each alliance from the perspectives of both parties, the BeKi has four separate versions: two for the therapist evaluating his/her alliance to the patient (BeKi therapist-patient) or parent (BeKi therapist-parent), and one each for the patient (BeKi patient) and the parent (BeKi parent) evaluating their respective alliances to the therapist.

(3) Moreover, we will assess the parent rating of adaptive and maladaptive emotion regulation strategies (FRUST parents, see above) [51].

(4) Additionally, after every therapy session, we will assess treatment adherence as a mediator using the Adherence Questionnaire. Four different items will be used to operationalize adherence as the child’s cooperation during the therapy session and adherence as the implementation of therapy homework. For this study, a modified version of the Adherence Questionnaire [42] will be used. Internal consistencies of the original Adherence Questionnaire range between α ≥ 0.95 or α ≥ 0.95 for children and α ≥ 0.97 or α ≥ 0.97 for parents [13, 14].

#### Sample size

A total number of 70 children 35 / 35 between the ages of 6;0 and 12;11 will be included in this exploratory study. To date, the effects of smartphone-augmented CBT on the implementation of therapy homework in children with aggressive behavior have barely been investigated. Other explanatory studies refer to an even a smaller number of cases [15, 23]. As the AUTHARK study aims to provide a basis for preparing a subsequent multicenter trial, the sample size needed is not based on formal power calculations. Instead, a sample size is proposed that allows us to precisely estimate the variance of critical outcome parameters that can then be entered into a power calculation for a confirmatory trial. In this way, the overall sample size for the main RCT can be minimized [74].

Based on results from the previous literature, we assume a small to moderate effect size (Cohen’s d ~ 0.4) [75], for which approximately 30 participants per treatment arm for a pilot randomized trial are recommended [74, 76]. Furthermore, a study with a similar design, comparing two groups across four assessment points (pre-, post-, and follow-up measurements), expects moderate effects regarding the app’s influence on therapy homework with a sample size of *n* = 35 per group [16]. Moreover, the power of a sample can be increased by a high number of measurements per patient [77]. In our study, THA will be measured at least eight times over a period of approximately sixteen weeks. At each assessment, the patients will be asked to use the smartphone app for five consecutive schooldays. Based on previous trials with a similar patient population and interventions, a dropout rate between 10 and 15% is expected [78]. Therefore, *n* = 35 patients per group (total: *n* = 70) should be recruited.

#### Data management and confidentiality

Most of the trial data will be assessed electronically through an online survey tool (LimeSurvey) [79]. After the completion of an assessment point, the stored data will be exported from the platform by a designated employee and saved in an encrypted data network. For each assessment point, the data will be organized according to patient-, caregiver-, and teacher ratings (see above).

The primary outcome of the trial, the THA, will be assessed weekly using the Adherence Questionnaire (see above), which will be completed by the therapists in a paper-and-pencil form in both groups. The data will then be re-entered digitally by one designated employee. The data will be regularly reviewed for completeness, consistency, and plausibility by two members of the project. After each assessment week, the data from the AUTHARK smartphone app (video diary, momentary assessment function) will be exported, transferred and saved to an encrypted network, to which only selected project members will have access.

At the beginning of the study, all participants will receive an individual study identification number. Data collected within the study will be anonymized and can only be associated with the patient by the project staff through the study identification number. Legal regulations for data protection will be fulfilled. All participating families and teachers will be informed about their rights in terms of data storage, data protection, and data deletion.

Informed consent will be obtained both in both written and verbal form from patients, parents/caregivers or guardians, and (if applicable) teachers before screening. For detailed information, see Additional file 2: Model written informed consent. All participants will be able to clarify questions about the study with research staff members. To participate in the study, it is required that both the patient and his/her parents/caregivers or guardians give their assent and informed consent. Likewise, teachers must give their informed consent for study participation. Data entry and processing will take place as soon as signed informed consent is available.

This study is designed as a small monocenter pilot study with no external funding, and there will be no external data monitoring or auditing committee, although this will be considered for a subsequent larger trial.

#### Statistical analyses

##### Patient demographics/other baseline characteristics

Demographic and other baseline data will be obtained at T1 and will be summarized descriptively for all documented patients. Continuous data will be summarized by arithmetic mean, standard deviation, minimum, 25% quantile, median, 75% quantile, maximum, and the number of complete and missing observations. If appropriate, continuous variables can also be presented in categories. Categorical data will be summarized according to the total number of patients in each category and the number of missing values. Relative frequencies will be displayed as valid % (number of patients divided by the number of patients with non-missing values).

##### Analyses of primary endpoint

The primary (full) analysis set is derived from the intention-to-treat (ITT) principle (all patients randomized with a valid baseline assessment). Additionally, per protocol analyses will be conducted based on all patients with at least 50% of the planned treatment sessions and a valid follow-up. As primary endpoint, the overall scores on THA will be calculated from the baseline, intermediate, and final assessment points (T1, T2, T3). THA scores assessed after each session will also be included in the analyses. A mixed model repeated measures multivariate analysis of variance will be performed with the between factor Group (smartphone-augmented vs. traditional), the within factor Time (baseline, first treatment phase, intermediate assessment, second treatment phase, final assessment) and the two-way interaction of Group x Time.

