##### Analyses of secondary endpoints

Secondary outcomes will be analyzed using either mixed models for repeated measures (heterogeneous first-order autoregressive structured covariance matrix over time) or generalized estimating equation approaches with corresponding marginal means and contrast tests (multilevel modeling). Time-to-dropout distributions will be summarized by the Kaplan–Meier method and compared using the (stratified) log-rank test. All efficacy variables will be summarized by time point and treatment arm (mean, standard deviation, percentiles (i.e., minimum, 25^th^, 50^th^, 75^th^, and maximum), count, percentage). Moreover, moderation, mediation and conditional process modeling [80] will be conducted based on regression and structural equations (interaction, simple slope analysis; direct/indirect effects, kappa squared).

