##### Missing values

It should be emphasized that as few patients as possible should discontinue treatment and that all patients should be followed up and documented after discontinuation of the treatment in order to record data required according to the ITT principle. To assess the impact of up to 20% attrition, multiple imputation approaches will be taken, accounting for proxy measures and assuming specific missingness-not-at-random patterns. Sensitivity analysis with a data set with and without imputation will be computed to assess the effects of missing values. The details will be documented in a statistical analysis plan. The analysis of subjects essentially observed and treated per protocol is supportive.

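### The primary THA test carries a label that permits a complete-vector MANOVA, which conflicts with the ITT set; one likelihood mixed model of post-baseline scores should be named instead

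*Protocol article*

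**What the plan says.** All places are in the protocol article.

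- **Analyses of primary endpoint**, analysis set: "The primary (full) analysis set is derived from the intention-to-treat (ITT) principle (all patients randomized with a valid baseline assessment".
- **Analyses of primary endpoint**, test: "A mixed model repeated measures multivariate analysis of variance will be performed with the between factor Group" (two arms), together with "the within factor Time (baseline, first treatment phase, intermediate assessment, second treatment phase, final assessment" and the Group by Time interaction. No covariance structure or estimation method is given.
- **Analyses of secondary endpoints**, opening sentence: "Secondary outcomes will be analyzed using either mixed models for repeated measures (heterogeneous first-order autoregressive structured covariance matrix over time". The alternative offered there is a GEE approach. A mixed model with a stated covariance structure is thus named for secondary outcomes only.
- **Missing values**: "all patients should be followed up and documented after discontinuation of the treatment in order to record data required according to the ITT principle". To gauge the effect of attrition of up to 20%, "multiple imputation approaches will be taken, accounting for proxy measures and assuming specific missingness-not-at-random patterns". Then: "Sensitivity analysis with a data set with and without imputation will be computed to assess the effects of missing values". Which data set is primary is not stated, and the details are left to a statistical analysis plan.
- **Sample size**: about 30 per arm are recommended, "a dropout rate between 10 and 15% is expected", and 35 per arm are to be recruited. The size does not rest on a formal power calculation.
- **Primary outcome**: homework is first assigned at session 2. The THA score is the ratio of completed to requested diary entries multiplied by a quality rating.

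**The concern.** A multivariate ANOVA needs a full vector of responses from each child. A child who leaves in treatment phase 2 is then removed entirely, including the THA already recorded in phase 1. That is not an analysis of all randomised children with a valid baseline. The words mixed model do not settle the matter: together with a between factor and a within factor, they are also the ordinary vocabulary of a mixed-design ANOVA.

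The pilot is meant to supply variance estimates for a confirmatory trial, and the Sample size section appeals to the many measurements per child. A complete-vector analysis discards exactly those measurements for every partial completer. If dropout is related to adherence differently in the two arms, the group difference is distorted as well.

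**Working it through.** **1. The article's own figure.** Inflating 30 per arm for dropout:
- 10%: 30/0.90 = 33.3, so 34
- 12.5%: 30/0.875 = 34.3, so 35
- 15%: 30/0.85 = 35.3, so 36

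The stated 35 per arm reproduces.

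**2. Children lost to listwise deletion (of 70).**
- 10% dropout: 70 × 0.10 = 7 lost, 63 kept
- 15%: 70 × 0.15 = 10.5 lost, 59.5 kept
- 20% (the attrition named under Missing values): 14 lost, 56 kept

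Isolated gaps remove more. Suppose, as an assumption, that 5% of values are missing independently at each of the 4 post-baseline levels. Then 70 × 0.95⁴ = 57.0 remain, and with 15% dropout as well 57.0 × 0.85 = 48.5. With 2% and 10% missing per level, 64.6 and 45.9 remain before dropout. If a level averages several weeks, one missing week does not empty it, so these figures apply to missing levels.

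**3. Precision.** Illustrative power for a single comparison at the article's d = 0.4, with an assumed two-sided alpha of 0.05, is Φ(0.4·√(n/2) − 1.96):

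| n per arm | dropout | power |
|---|---|---|
| 35 | none | 0.387 |
| 31.5 | 10% | 0.355 |
| 29.75 | 15% | 0.338 |
| 28 | 20% | 0.322 |

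**4. Bias, closed form.** If dropouts score lower than completers by a gap g (in SD), the completer-only difference is off by (app dropout − control dropout) × g when g is equal in both arms. With 10% app and 15% control dropout, and assumed gaps of 0.5, 0.8 and 1.0, this is −0.025, −0.04 and −0.05 SD. With equal dropout it is zero. With heavier dropout in the app arm the sign reverses. For scale, the standard error of one standardised comparison with 35 per arm is √(2/35) = 0.24.

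**5. Bias, simulation.** Assumptions not in the article: 4 post-baseline levels, SD 1, within-child correlation 0.6, true difference 0.40, 35 per arm, dropout depending on the previous score where stated, 3,000 replicates.

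| Dropout mechanism | Kept, control / app | Complete cases: mean (SD) | Likelihood: mean (SD) |
|---|---|---|---|
| Random in both arms | 85% / 85% | 0.40 (0.217) | 0.40 (0.202) |
| Low THA, similar in both arms | 84% / 87% | 0.39 (0.207) | 0.40 (0.203) |
| Low THA, heavier in control | 75% / 91% | 0.30 (0.213) | 0.40 (0.209) |
| Low THA in app arm only, random in control | 85% / 84% | 0.51 (0.214) | 0.40 (0.206) |

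The complete-case estimate is less precise in all four rows. It is biased by more than about 0.01 only in the last two, and there in opposite directions. The third row needs about 25% dropout in control, above the article's expected range.

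**6. The baseline level.** Time has five levels, the first being baseline, and the Participant timeline section also lists THA among the T1 measurements. Diary entries are not requested before session 2, so no diary-based THA can exist at T1. A literal five-level complete-vector analysis would contain no child.

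**The case against.** The strongest reply is that the label also contains the words mixed model, so a likelihood model that keeps partial data may be intended. In addition, the ITT set is declared primary, per-protocol analysis is only supportive, and multiple imputation is planned. On imputed data even a MANOVA keeps every randomised child. Missing-data details are left to an analysis plan that is not shown.

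Much of this stands. A reader might infer that the primary analysis is a completers-only analysis that loses the least adherent children and so shrinks the app effect. The article does not support that. Pure MANOVA is one reading of an ambiguous label. Nothing says that the unimputed data are primary. No section links dropout to THA or expects it to differ by arm. The bias can be nil, negative or positive. Nor is the step from 30 to 35 per arm evidence of listwise deletion, since dropouts cost information under any model.

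What does not stand is that the point can wait. The deferral covers missing-data details, whereas the primary model is fixed in the article, in words that permit a method at odds with its own analysis set. The imputation is framed as assessing the impact of attrition, with a comparison of imputed and unimputed results described as sensitivity analysis, so it does not define the primary analysis. Follow-up after discontinuation can recover questionnaires but hardly THA, because a child who no longer attends sessions has no requested entries to form the ratio.

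**Conclusion.** The point holds as a badly fixed primary model. The label permits a repeated-measures MANOVA, and on unimputed data that method conflicts with the ITT set. Under that reading, 7 to 14 of 70 children and their observed scores are lost at 10 to 20% attrition, and more if whole levels are missing. Illustrative power falls from 0.387 to between 0.355 and 0.322. This is a modest loss in a pilot not sized on power, but an avoidable one.

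Bias is conditional. It is near zero if dropout is random or similar across arms, and about −0.10 to +0.11 SD in the simulated cases where adherence-related dropout differs by arm. Those cases rest on assumed mechanisms and an assumed correlation. The closed form at 10% against 15% dropout gives at most 0.05 SD for gaps up to 1 SD, about a fifth of one standard error.

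The baseline Time level is a defect under any reading of the label, because diary-based THA does not exist at T1.

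**What to change.** In Analyses of primary endpoint, replace the current label with one method, for example:

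> The primary analysis is a likelihood-based linear mixed model for repeated measures of all observed post-baseline THA scores, with Group, post-baseline Time and Group × Time as fixed effects and a named within-child covariance structure. No child is removed because of missing homework weeks. Randomised children without any THA score enter through the planned multiple imputation. Imputation under missing-not-at-random patterns is the sensitivity analysis.

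Remove baseline from the Time levels and bring the statement about THA at T1 in the Participant timeline section into line. A complete-vector analysis, if wanted, can be reported as supportive.

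The cost is a few lines of text. The model class is already named for secondary outcomes, and no new data, patients or assessments are needed. The downside is reliance on a missing-at-random assumption, which the sensitivity analysis already planned would probe.
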